## Abstract

**Background:**

Reducing patient length of stay is a high priority for health service providers. Preliminary information suggests additional Saturday rehabilitation services could reduce the time a patient stays in hospital by three days. This large trial will examine if providing additional physiotherapy and occupational therapy services on a Saturday reduces health care costs, and improves the health of hospital inpatients receiving rehabilitation compared to the usual Monday to Friday service. We will also investigate the cost effectiveness and patient outcomes of such a service.

**Methods/Design:**

A randomised controlled trial will evaluate the effect of providing additional physiotherapy and occupational therapy for rehabilitation. Seven hundred and twelve patients receiving inpatient rehabilitation at two metropolitan sites will be randomly allocated to the intervention group or control group. The control group will receive usual care physiotherapy and occupational therapy from Monday to Friday while the intervention group will receive the same amount of rehabilitation as the control group Monday to Friday plus a full physiotherapy and occupational therapy service on Saturday. The primary outcomes will be patient length of stay, quality of life (EuroQol questionnaire), the Functional Independence Measure (FIM), and health utilization and cost data. Secondary outcomes will assess clinical outcomes relevant to the goals of therapy: the 10 metre walk test, the timed up and go test, the Personal Care Participation Assessment and Resource Tool (PC PART), and the modified motor assessment scale. Blinded assessors will assess outcomes at admission and discharge, and follow up data on quality of life, function and health care costs will be collected at 6 and 12 months after discharge. Between group differences will be analysed with analysis of covariance using baseline measures as the covariate. A health economic analysis will be carried out alongside the randomised controlled trial.

**Discussion:**

This paper outlines the study protocol for the first fully powered randomised controlled trial incorporating a health economic analysis to establish if additional Saturday allied health services for rehabilitation inpatients reduces length of stay without compromising discharge outcomes. If successful, this trial will have substantial health benefits for the patients and for organizations delivering rehabilitation services.

**Clinical trial registration number:**

Australian and New Zealand Clinical Trials Registry ACTRN12609000973213

## Background

Reducing patient length of stay is a high priority for health service providers and is considered to be an indicator of efficiency [1,2]. The implications of a reduction in length of stay are potentially significant for the individual, the health service and for the community. A reduction in length of stay means the individual can return to their community sooner, that individuals may not have to wait so long for a bed, that the health service can treat more patients, and that there are cost savings for the community. However, from the perspective of the health system, if reducing length of stay is achieved at the expense of quality of care, this will reduce efficiency and could increase pressures and costs to other health services. Despite this concern, there is some evidence, at least in acute hospitals, that reducing length of stay has not been achieved at the expense of quality of care [3,4].

The allied health team, including physiotherapists and occupational therapists, play a key role in the effective management of patients receiving rehabilitation for neurological and musculoskeletal conditions [5-10]. Physiotherapy and occupational therapy aim to increase the independence of patients receiving rehabilitation by improving mobility and self-care skills. Developing independent mobility and self care skills are important physical factors in predicting the need for long-term placement [11] and are associated with better quality of life [12]. Therefore, attaining mobility and self-care skills are important in determining whether patients receiving rehabilitation can successfully return home to participate in their usual societal activities and improve their quality of life.

There has been an increased focus on the importance of intensity and activity in rehabilitation. During early rehabilitation, patients receive relatively little therapy and have low levels of physical activity [13]. Reports that increasing the intensity of rehabilitation could be associated with improved outcomes [14] have led to calls for rehabilitation to be more active and intensive [15,16]. Previous studies have indicated that the intensity of physiotherapy and occupational therapy provision may affect patient outcomes leading to reduced mortality following stroke [17], and improved functional status following brain injury [18], stroke [17,19], and femoral fracture [20].

One way to increase the intensity of rehabilitation is to provide additional allied health services. Typically, allied health rehabilitation services are provided Monday to Friday. Weekend services have not been provided, have been provided on a much reduced scale, or have only been provided to patients at risk of an acute event such as due to a chest infection [21-24]. A recent systematic review provided preliminary evidence that additional allied health services can reduce length of stay in hospital for patients receiving rehabilitation [25]. There was evidence that additional weekend physiotherapy significantly decreased length of stay for patients who had undergone elective hip and knee joint arthroplasty [26] and patients with non-surgical stroke [27]. However, trial quality in the systematic review was only fair, with only three of nine included studies using a randomised control design.

Our pilot study examined the effect of additional Saturday physiotherapy for rehabilitation inpatients [28]. Two hundred and sixty two participants were included in this randomised controlled trial. The mean patient length of stay was 24.4 days (SD 15.9) for patients who received a Monday to Friday physiotherapy service and 21.2 days (SD 14.0) for patients who received a Monday to Saturday service. The 3.2 day difference demonstrated a trend in favour of the intervention group (95% CI -0.5 to 6.9 days, *p*= 0.09). Assuming a maintained effect size of 0.21 and power of 0.80, then 356 participants would have been required in each group to reach statistical significance.

Patient quality of care was not adversely affected by a shortened hospital stay [28]. There were no differences in function, quality of life and discharge outcomes between the Monday to Friday service and the Monday to Saturday service. Quality of life was not significantly different between the groups at discharge or at follow-up. There was no significant difference between groups in the change from admission to discharge for the secondary outcome measures of functional independence measure, timed 10 metre walk test, timed up and go, and the modified motor assessment scale. There were also no significant differences in discharge destination, adverse events or follow-up therapy between the groups.

In a healthcare system with fixed capacity even a small saving in length of stay can be important. The Australasian College for Emergency Medicine recently reported that if a hospital with 20,000 admissions each year saved half a bed day per patient by improving discharges, about 2000 extra patients a year could be admitted [29]. Data from our pilot study suggests that if the average length of stay from each rehabilitation episode was reduced by 3.2 days, there would be an additional 68 patients admitted to a typical 30-bed rehabilitation facility each year [28]. These results have the potential to increase patient flow from the acute to the subacute setting providing increased capacity in the acute care setting. A rigorous health economic evaluation in a larger trial is required to confirm the cost effectiveness of providing additional allied health services for rehabilitation.

In summary, to evaluate the potential benefits of the provision of additional Saturday allied health services to rehabilitation inpatients, we will conduct a fully powered randomized controlled clinical trial that will: complete an economic analysis of additional allied health services compared with the traditional Monday to Friday usual care service from a healthcare system perspective; and incorporate occupational therapy rehabilitation services in addition to physiotherapy.

The primary aim of this trial is to determine if the provision of additional Saturday allied health services will reduce the costs of care by reducing patient rehabilitation length of stay without affecting health related quality of life and functional outcomes compared to those receiving usual care. The secondary aims are to examine if the provision of additional Saturday allied health services has any effect on therapeutic functional goals at discharge; or the use of community-based health services post discharge from the sub-acute hospital setting, compared to those receiving usual care. For the purpose of this clinical trial the term "allied health" will specifically refer to physiotherapy and occupational therapy services.

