## Data analysis

### Sample size estimation

Sample size estimation is based on rehabilitation length of stay data [28]. For length of stay, with a maintained effect size of .21 and power of 0.80 a sample size of 356 participants in each group is required (total of 712 participants).

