### Statistical analysis

Between group differences of the primary outcomes (length of stay, EuroQol, and FIM) will be analysed with analysis of covariance of discharge scores with the baselines score as covariate [45]. Intention to treat analysis will be used with any missing health outcome data imputed using the last value carry forward method [46].

A rigorous economic evaluation will be carried out alongside the randomised clinical trial. Cost effectiveness of the intervention will be determined as the incremental cost of additional Saturday allied health inpatient rehabilitation services compared to usual inpatient rehabilitation per quality adjusted life year saved. The primary measure of incremental effect for the economic evaluation will include the difference in health related quality of life between the control and treatment groups using the EuroQol. A secondary incremental cost effectiveness ratio will be determined using the cost per change in functional status using the FIM.

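### The primary aim promises no effect on quality of life and function, but EuroQol and FIM get only a difference test with no margin, and the sample size covers length of stay alone

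*Protocol article*

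**What the plan says.** The last paragraph of the Background in the protocol article sets a two-part primary aim: lower costs through a shorter stay, "without affecting health related quality of life and functional outcomes compared to those receiving usual care". The Abstract's Discussion describes a fully powered trial to establish whether the service "reduces length of stay without compromising discharge outcomes", and the main Discussion repeats this. The Abstract's Background puts the question differently: whether the service "reduces health care costs, and improves the health of hospital inpatients receiving rehabilitation".

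On outcomes, the Abstract states: "The primary outcomes will be patient length of stay, quality of life (EuroQol questionnaire), the Functional Independence Measure (FIM), and health utilization and cost data". On analysis, the Statistical analysis section states: "Between group differences of the primary outcomes (length of stay, EuroQol, and FIM) will be analysed with analysis of covariance", applied to discharge scores with the baseline score as covariate and missing health outcomes filled by carrying the last value forward. On size: "Sample size estimation is based on rehabilitation length of stay data", and "with a maintained effect size of .21 and power of 0.80 a sample size of 356 participants in each group is required", which makes 712 for the two arms together.

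The article gives no margin, no equivalence or non-inferiority hypothesis, and no rule based on a confidence interval for EuroQol or FIM.

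**The concern.** The article fixes an aim, a test and a basis for the sample size, and the three do not fit together. A difference test can show that the arms differ. It cannot show that they do not, because failing to reject may only reflect limited precision. Half of the primary aim therefore has no analysis that could support it.

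The two statements of the aim also need different hypotheses: improved health is a superiority claim, and unaffected health is a non-inferiority or equivalence claim.

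At stake is the trial's main message, a shorter stay at no cost to patients. The Background itself raises the worry that shorter stays might be bought with poorer care. Its account of the pilot (262 participants) also shows how easily the step is taken: non-significant comparisons of function and quality of life are reported there as an absence of differences, and as care not having suffered.

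**Working it through.** **Inputs.** From Sample size estimation: standardised effect 0.21, power 0.80, 356 per arm. Assumed: two-sided 5%, which the article does not state; it reproduces the published figure, whereas one-sided 5% gives 281. Also assumed: deficits and margins in SD units, because the article gives neither an SD nor a margin for FIM or EQ-5D, and a baseline correlation of 0 or 0.6.

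**1. The plan's own figure.** n per arm = 2 × (zα + zβ)² ÷ d², with zα = 1.960, zβ = 0.842 (unrounded in the calculation) and d = 0.21. This gives 2 × 7.849 ÷ 0.0441 = 356, so 712 in total. The figure reproduces. It concerns length of stay only.

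**2. Precision for EuroQol or FIM.** SE of the standardised difference = √(2 ÷ 356) = 0.0749, so the 95% half-width is 1.96 × 0.0749 = 0.147 SD. With baseline correlation 0.6 the SE is multiplied by √(1 − 0.36) = 0.8, giving 0.0600 and a half-width of 0.118 SD. Without covariate gain, a just non-significant deficit of almost 0.147 SD has a confidence limit near 2 × 0.147 = 0.29 SD.

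**3. Chance that a true deficit d is non-significant.** P ≈ Φ(1.96 − d/SE).

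| True deficit | No covariate gain | Baseline correlation 0.6 |
|---|---|---|
| 0.10 SD | 73% | 62% |
| 0.15 SD | 48% | 29% |
| 0.21 SD | 20% | 6% |

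Example: 0.10 ÷ 0.0749 = 1.33, and Φ(1.96 minus 1.33) = 0.73. Last cell: 0.21 ÷ 0.0600 = 3.50, and Φ(1.96 minus 3.50) = 0.06.

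**4. Non-inferiority on one outcome at true equality** (one-sided 2.5%, no covariate gain). Power = Φ(margin/SE − 1.96) with SE = 0.0749: 27% for a margin of 0.10 SD, 52% for 0.15, 76% for 0.20, 80% for 0.21, 92% for 0.25 and 98% for 0.30. For 80% power, a margin of 0.15 SD needs 698 per arm, a margin of 0.20 SD needs 393 and a margin of 0.25 SD needs 252.

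**5. The combined claim.** It needs length-of-stay superiority (80% at an effect of 0.21) and non-inferiority on both FIM and EQ-5D. Under independence, joint power = 0.80 × (single-outcome power)².

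| Margin | No covariate gain | Baseline correlation 0.6 for FIM and EQ-5D |
|---|---|---|
| 0.20 SD | 0.80 × 0.761² = 46% | 67% |
| 0.21 SD | 0.80³ = 51% | 70% |
| 0.25 SD | 0.80 × 0.916² = 67% | 78% |
| 0.30 SD | 0.80 × 0.979² = 77% | 80% |

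Length of stay is held at 80% in both columns, so joint power cannot exceed 80%. Correlation between the outcomes would move these figures.

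**The case against.** **The detail may sit elsewhere.** A journal article condenses a fuller document, and margins can be set in an analysis plan. That would answer a complaint of mere silence. It does not answer a mismatch between an aim, a test and a sample-size basis that the article itself states.

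**The misreading is not planned.** No rule in the article says that p>0.05 will be taken as proof of no harm. A reader might infer this from the pilot account, but that account is not a decision rule for this trial. What stands is narrower: the planned test cannot support the stated aim.

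**The economic analysis offers some protection.** It carries the estimated EuroQol and FIM differences into its ratios whatever their significance, and varies both in sensitivity analysis. A real loss would show there. This mitigates the consequence but supplies no criterion for the clinical claim.

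**The small deficits are chosen, not documented.** The article does not say that 0.10 or 0.15 SD matters clinically. At 0.21 and 0.25 SD the difference test misses a deficit only about 20% and 8% of the time. This is fair, and it is why a justified margin is needed.

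**Stronger readings to avoid.**
- A reader might infer an inflated family-wise error from several primary outcomes. That requires a rule under which any single outcome means success. The article states no such rule, and its aim is a conjunction. Cost is handled in the economic analysis.
- A reader might take 712 as sufficient because one outcome reaches 80% power at a 0.21 SD margin. The combined claim does not.
- A reader might take the article's 10% change in functional independence as a ready margin. It is the unit of a cost-effectiveness ratio, not a tolerable loss.

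**Conclusion.** The point holds. The stated analysis of EuroQol and FIM cannot support the no-effect half of the primary aim, and the Abstract's superiority wording conflicts with that aim. The sample size is correct for length of stay but says nothing about the full aim.

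The size depends on what deficit matters. With no covariate gain, deficits of 0.10 to 0.21 SD would go undetected in 73% to 20% of trials. Joint power for the combined claim is 46% to 77% over margins of 0.20 to 0.30 SD, or 67% to 80% with a baseline correlation of 0.6. These are ranges under assumptions (two-sided 5%, independent outcomes, true equality on FIM and EQ-5D), not estimates for this trial.

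**What to change.** 1. Align the Abstract's Background with the primary aim, so that one hypothesis is stated for quality of life and function.
2. Before outcome data are seen by allocation, set justified non-inferiority margins for FIM and the EQ-5D index at discharge, the time point of the planned analysis of covariance.
3. Allow the no-harm claim only if the confidence limit from that analysis lies on the acceptable side of the margin, and never from p>0.05.
4. Define the combined claim as length-of-stay superiority together with both non-inferiority results. Because all three must hold, no alpha split is needed.
5. Check the non-inferiority result under another missing-data method. Carrying a baseline value forward may pull the arms together, which favours a finding of no difference.
6. Restate power for the combined claim once the margins and SDs are known.
7. If no margin can be agreed, drop the no-effect conclusion and report estimates with confidence intervals.

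The cost is agreement on two margins, a revised power statement and one additional sensitivity analysis. Whether 712 remains adequate depends on the margins. The no-harm claim becomes harder to make, and the stated power for the full aim will be lower than 80% or at best about equal to it.

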## Methods/Design

### Research design

The research design is a single blinded randomised controlled trial of additional Saturday allied health services for rehabilitation inpatients compared with the comparison group receiving a Monday to Friday usual care allied health service. We will conduct a clinical trial, incorporating an economic analysis, across two rehabilitation facilities with approximately 90 rehabilitation beds (providing services to eastern metropolitan Melbourne, Australia). Participants in the comparison group will receive five days of allied health services (Monday to Friday) and participants in the intervention group will receive six days of allied health services (Monday to Saturday). The trial has received ethics approval from Eastern Health Ethics Committee and La Trobe University Faculty Human Ethics Committee.

### Participants

Participants will be included if they are:

• aged 18 years or older

• have been admitted for rehabilitation at either of the two rehabilitation facilities.

Participants will be excluded if they

• do not give informed consent to participate in the trial, or

• if they are admitted for geriatric evaluation and management, as this patient group are managed differently to patients admitted for rehabilitation, or

• if they are already enrolled in another intervention trial.

Participants will not be excluded if their primary language is a language other than English. A language interpreter will be provided to ensure these patients understand the informed consent procedure and to assist them with the administration of the quality of life and clinical outcome measures. Participants will not be excluded if assessment indicates reduced cognition, as indicated by a score of less than 24/30 on the Mini-mental State Examination [30] since cognitive impairment is common in patients receiving rehabilitation [31]. Our pilot data found that 24% of patients admitted for rehabilitation had severe cognitive impairment [28]. Written informed consent will be sought from all eligible patients admitted for rehabilitation. For patients with impaired cognition or aphasia, the next of kin will be approached for informed consent.

### Randomisation

Participants will be randomised to the additional allied health services (intervention) group or the control group with a concealed method, using permuted blocks of 4, 6 and 8, stratified for case-mix status (neurological and other/orthopaedic) and site (two sites). Stratification will include site in order to facilitate the staffing of the Saturday service. The block allocation sequence will be generated by http://www.randomization.com and assignments sealed in sequentially numbered opaque envelopes. Only after the participant has enrolled in the trial and completed written informed consent and baseline testing will assignment be made by the project officer by opening the next envelope in the sequence. A member of the research team who is not involved in participant recruitment, assessment or treatment will be responsible for preparing the envelopes.

### Intervention

Usual care physiotherapy and occupational therapy will be provided to participants in the control group daily from Monday to Friday. The specific intervention will be at the discretion of the treating therapists.

The intervention group will receive the same amount of intervention as the control group Monday to Friday, plus a full service on Saturday, equating to an additional one hour of physiotherapy and one hour of occupational therapy. The type of intervention provided at the weekend will be decided by the patient's regular physiotherapist and occupational therapist, and instructions will be provided via a written handover to the weekend therapist administering the additional treatment. Provision will be made to ensure that if a participant in the control group required urgent physiotherapy at the weekend that it would be provided as normal, for example if they developed an acute respiratory complication requiring cardiorespiratory physiotherapy.

### Outcome measures

Blinded assessors will complete the baseline, discharge and follow-up assessments. The success of blinding will be evaluated at the final assessment by asking assessors to estimate their patient group allocation. During the pilot trial assessors correctly guessed group allocation of the intervention group in 61% of cases and of the control group in 64% of cases [28].

